### Methods in analysis to handle protocol non-adherence and any statistical methods to handle missing data {20c}

Intention to treat analysis will be performed. Per-protocol analysis is going to be applied to compare the results in a sensitivity analysis.

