The focus of these three aftercare rehabilitation programs (T-RENA, IRENA, and Reha-Sport) is on physiotherapy, movement, and behavioral therapy modules; however, they lack personalization of therapy content regarding individual needs. Furthermore, all three are conducted in an ambulatory setting and follow the routine of the German Pension Insurance aftercare program.

At the end of the rehabilitation at the clinic, one or none of the aftercare programs is recommended [29]. If the patient is unable to attend the rehabilitation center, the patient does not receive any aftercare treatment.

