### Strategies to improve adherence to interventions {11c}

One of the strategies to improve adherence to the interventions is to schedule training sessions by assigning electronic appointments. This strategy supports the “follow-up adherence,” which refers to the completion of the scheduled assessment measures [30]. The procedure was already successfully tested and implemented in the pilot study (material unpublished), and it will be achieved in the study again with the help of the scheduling department of the rehabilitation clinic.

The study therapist is at the clinic at least 3 days per week and once after the discharge of the last participant. He/she is also available by telephone at fixed times during the first 12 weeks of intervention to support all participants. This strategy intends to reduce misunderstandings about training regimens [30].

Moreover, at the first session, participants in the intervention group receive a training journal and an exercise booklet to improve the adherence to the intervention. Self-reporting diaries are a common measure of adherence in clinical trials [31]. Besides, the training journal is used to monitor adherence and the participant will return it at the end of the follow-up home-based training (T3).

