##### Patient compliance and acceptance

To measure patient compliance to the intervention program (therapy adherence), the frequency of sensorimotor training, patient education activities, and the use of body scan is registered in the training journal. This frequency may range from zero to three times weekly during 24 weeks. Further, the level of sensorimotor training difficulty is recorded as well as the degree of pain before and after exercises, using the 11-point *Numeric Rating Scale*. Additionally, a self-designed question “How often do you perform the aftercare exercises?” will be asked to all participants at T2 and T3 in order to have a subjective assessment of patient compliance.

The level of acceptance of the program will be assessed using self-developed question blocks (blocks represent the constructs defined through a factor analysis in the pilot study). The constructs are satisfaction with the program (it includes the questions “How satisfied are you with your aftercare program?” and “How do you rate the effect of the program you have completed?” from T2 and T3, Likert scale 0–10), self-competence acquired to continue with the program after the center-based rehabilitation stay (it consists of 8 questions from T1 such as: “How convinced are you that you will be able to use the learned exercises after the rehabilitation stay?”, “How well prepared do you feel with regard to time after rehabilitation stay?” and “How helpful did you find the preparatory exercises during rehabilitation stay?”, Likert scale 0–10), and sustainability (including “How confident are you that you will continue to use your aftercare program regularly?” from T2 and T3, Likert scale 0–10, and open questions as “What could stop you from continuing the exercises?”).

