## Statistical methods

### Statistical methods for primary and secondary outcomes {20a}

Data is analyzed at the end after T3 data collection completion. Then, an examination of underlying assumptions for parametric or non-parametric hypothesis testing is applied. For the primary outcome pain (DISS, CPI), an analysis of variance (ANOVA) repeated measures for three time points (T0, T2, T3) between the groups (intervention vs control group) with covariates adjustment is planned. The covariates to include in the analysis are center, age, and sex. A complete case analysis is intended.

For secondary outcomes (psychometric items), missing value imputation follows only (in case of psychometric scores) the specific test manuals. Likewise, variance analytical testing is proposed. A sensitivity analysis is planned for concomitant therapy, such as medications.

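### A per-protocol set built on training adherence would compare selected intervention patients with largely unselected controls, so it should not serve as the check on the intention-to-treat result

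*Protocol article*

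**What the plan says.** Protocol article, section {20c}: "Intention to treat analysis will be performed", and then "Per-protocol analysis is going to be applied to compare the results in a sensitivity analysis". The article does not define the per-protocol set. Section {20a} adds, for the primary outcomes, "A complete case analysis is intended".

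On adherence in the intervention arm, section {11c} says that "participants in the intervention group receive a training journal and an exercise booklet to improve the adherence to the intervention" and that "the training journal is used to monitor adherence". Under Patient compliance and acceptance, "the frequency of sensorimotor training, patient education activities, and the use of body scan is registered in the training journal". These are all components of the study programme. The same paragraph puts one self-designed question, on how often the aftercare exercises are done, to participants of both arms at T2 and T3, and calls the result subjective.

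On the control arm, section {11a}, Control group: "At the end of the rehabilitation at the clinic, one or none of the aftercare programs is recommended". A control who cannot get to a center receives no aftercare. No minimum attendance is given for any of the three standard programmes. Table 2 lists the aftercare recommendation from the discharge report, but no record of attendance.

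Section {11b} allows a change of arm at T0 in either direction, at the patient's explicit request.

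**The concern.** A per-protocol comparison is informative only if the same kind of exclusion can be applied in both arms. Here an intervention patient who does no training is a non-adherer, while a control who does no aftercare may still be receiving exactly the described control condition. A filter on training would therefore act almost entirely on one arm.

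Patients who keep up home training for weeks probably differ in prognosis from those who stop, and some will stop because of pain, which is the outcome. Removing them leaves a better-prognosis intervention group against nearly the whole control group. The comparison is then no longer randomised, and its likely error favours the programme. The trial is open and is a superiority trial (sections {17a} and {8}), and its result may inform routine aftercare (section {31a}). A reader could take a larger per-protocol effect as support for the programme when it only reflects selection.

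**Working it through.** **Step 1. What could define adherence in each arm.**

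| Source | Intervention | Control |
|---|---|---|
| Training journal | Sessions of study modules | Not issued |
| Exercise question at T2 and T3 | Yes, one subjective item | Yes, but unclear if no programme was given |
| Required amount of treatment | Study training schedule | One programme or none, no minimum |
| Change of arm at T0 | Possible | Possible |

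Only the last row can be applied alike in both arms, and it identifies switching, not training.

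**Step 2. Size of the distortion.** The protocol gives no figure for the per-protocol analysis, so there is none to reproduce.

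- From section {14}: 562 intervention patients, total 843, design effect d = 0.2, correlation among repeated measures 0.57. Controls are taken as 843 − 562 = 281. (The printed control figure is 289, which does not add up to 843. That is a separate matter.)
- Assumed, because the document gives neither: adherent share p from 0.5 to 0.9, and correlation r from 0 to 0.3 between adherence propensity and a good T2 outcome.
- Model: no treatment effect, standardised outcome, normal adherence propensity, intervention arm cut to its adherent share, controls left whole.

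Formulas, with z = Φ⁻¹(1 − p) and λ = φ(z)/p:

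- bias = r·λ
- variance among retained intervention patients v = 1 − r²·λ·(λ − z)
- SE = √(v/(562p) + 1/281)
- chance of a significant result favouring the programme = Φ(bias/SE − 1.96)

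Example, p = 0.5 and r = 0.3: z = 0, φ(z) = 0.399, λ = 0.798, so bias = 0.239. Then v = 0.943 and SE = √(0.943/281 + 1/281) = 0.083. The ratio is 2.88, and Φ(0.92) = 0.82.

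| p | λ | Bias in SD, r = 0.1 / 0.2 / 0.3 | Per-protocol result significant in favour |
|---|---|---|---|
| 0.5 | 0.798 | 0.08 / 0.16 / 0.24 | 16% / 48% / 82% |
| 0.7 | 0.497 | 0.05 / 0.10 / 0.15 | 9% / 25% / 49% |
| 0.9 | 0.195 | 0.02 / 0.04 / 0.06 | 4.5% / 8% / 12% |

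At r = 0 the bias is zero and the favourable rate is the nominal 2.5%. If both arms could be cut alike on a comparable criterion, the bias in this model would be about zero.

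**Step 3. Effect of baseline adjustment.** Suppose adherence correlates equally with the T0 and T2 scores. Adjusting for T0 at 0.57 multiplies the bias by 1 − 0.57 = 0.43 and the SE by √(1 − 0.57²) = 0.82. At p = 0.5 and r = 0.3, ignoring the small variance reduction, SE = √(1/281 + 1/281) = 0.084. The bias becomes 0.239 × 0.43 = 0.103 and the SE 0.084 × 0.82 = 0.069, so the 82% falls to about 32%. At r = 0.2 the 48% falls to about 17%. The upper rows of the table therefore describe adherence that is related to later outcome but not already reflected in the T0 score.

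**The case against.** The strongest reply is that the article never says that the journal defines the per-protocol set. A statistical plan exists (it is mentioned in section {19}) and may define the set. Excluding only patients who changed arm at T0 would fit section {20c} equally well. This stands, and it makes the point conditional on a set built on training adherence. A missing definition is not the complaint. The limitation lies in the control condition and the data collected, both fixed in the article, and no later definition can create non-adherence where the assigned care may be none.

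A reader might infer that only intervention patients can ever be excluded. The documents do not support that. Controls who change arm at T0 are off-protocol, and the exercise question, read with the discharge recommendation in Table 2, allows a crude criterion for controls who were given a programme. Neither balances a session-level filter in the other arm.

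A reader might also infer that the plan would falsely confirm a useless programme at the rates in the table. It would not. Those are rates for the per-protocol result taken alone. Confirmation also needs a favourable intention-to-treat result, which under no effect, with an unbiased main analysis, occurs about 2.5% of the time. In most of the other cases the two analyses would disagree, and a comparison of the two would show it.

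The assumed p and r also matter: at 90% adherence the problem is small.

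**Conclusion.** The point holds in conditional form. The adherence data are asymmetric by design, and a per-protocol set based on training would mix any programme effect with selection, probably in the programme's favour. Over the assumed ranges the bias is about 0.02 to 0.24 SD. It comes close to or exceeds the design effect of 0.2 only where roughly half to 60% adhere and the correlation is near 0.3. It vanishes if adherence is unrelated to prognosis, and it shrinks if adherence is also related to the T0 score and that score is adjusted for. The direction rests on the plausible but undocumented premise that patients who do worse train less.

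Intention to treat remains the main analysis, so the primary conclusion is not at risk from this source. What is at risk is an inflated or misleading secondary estimate, presented as a robustness check. The point merits a change to the plan but does not undermine the trial.

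**What to change.** Keep intention to treat as primary. If a per-protocol table is retained, label it descriptive and say that it is not a check of the primary result.

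Add a complier-average causal effect analysis with randomised arm as the instrument (two-stage least squares), adjusted for center and T0 score. Every randomised patient with outcome data stays in the arm assigned, so no adherence definition is needed for controls. Section {11b} offers controls part of the study materials only after they finish, so access to the programme in the control arm should be rare apart from T0 switchers, whom the same method accommodates.

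Define receipt preferably as the number of journal-recorded sessions up to T2, or as any training started. A high threshold fits badly: patients below it may still have had supervised sessions, materials and telephone support (section {11a}), so an assumption of no effect in them would be doubtful. State how missing journals are handled, since section {11c} has them returned only at T3 and patients who drop out may have none.

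The cost is some wording and one more model on data already planned for collection. With a yes/no definition of receipt, intervals widen by about 1/p: 1/0.7 = 1.4 times at 70% adherence and 1/0.5 = 2 times at 50%. The estimate relies on a self-reported journal and on the assumption that the offer has no effect without training. It also inherits any bias from the complete-case restriction.

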### Plans to give access to the full protocol, participant level-data, and statistical code {31c}

Does not apply. We do not contemplate access to the full protocol besides their publication. The datasets generated for this study should be available in the future after completion of the trial [doi is requested at the University of Potsdam]. The statistical code will remain in the internal files of the responsible parties.

## Oversight and monitoring

### Composition of the coordinating center and trial steering committee {5d}

The coordinating center is the Department of Medical Sociology and Psychobiology at the University of Potsdam, Germany. The overall project leader is the professor of the department, who takes the main decisions and communicates with the German Pension Insurance. A research assistant (master’s degree) has the responsibility of project coordination, involved in the communication with the partners (universities and institutes) and monitoring at the clinics. Further research associates (post-doctoral degree and master’s degree) are responsible for the intervention and data management, supported by students’ assistants at the department.

### Composition of the data monitoring committee, its role, and reporting structure {21a}

Two independent people with a master’s degree (employed at the Department of Medical Sociology and Psychobiology at the University of Potsdam, but not involved in the project work) participate in the monitoring committee. For the initial phase (2 weeks before trial first enrollment), 1–2 days per week include intensive monitoring at the rehabilitation clinic. It comprises location characteristics and internal processes implementation. Additionally, the therapist’s education/training includes study aims, documentation, and intervention training.

After the first participant enrollment, a written weekly report about the recruitment process and general questions from the therapists is scheduled. An online meeting with the therapists one time per month is outlined, as well as personal visits to the clinic once every 3 months.

Once a week, online data collection is reviewed to identify possible coding problems. The monitoring committee meets once every 2 weeks, supervised by the department’s professor. The data monitoring committee operates and reports directly to the department’s professor. The funder of the study is not involved in these processes and does not influence data collection or analysis.

### Adverse event reporting and harms {22}

The contact persons in case of such an event are both the study therapist and the corresponding physician in the clinic during the center-based phase (T0–T1) or the physician in the respective follow-up center (T2–T3). If the study therapist has been informed first about the adverse event, he/she immediately informs the physician. It is always the treating physician who decides whether to exclude the patient from the study.

### Frequency and plans for auditing trial conduct {23}

Each study center will be monitored once every 3 months by the study coordinator of the coordinating center.

### Plans for communicating important protocol amendments to relevant parties (e.g., trial participants, ethical committees) {25}

Do not apply. A specific meeting to communicate amendments to parties is not planned. However, in the quarterly network meetings, a synopsis on important changes and the trial process is discussed.

### Dissemination plans {31a}

A final report to the German Pension Insurance is planned. If successful, this intervention could be implemented in the regular aftercare of medical rehabilitation in Germany. The publication of the trial results in a scientific journal is also intended.

## Discussion

The main purpose of the study is to compare the efficacy of an individualized home-based aftercare program to the regular outpatient care for the rehabilitation of back pain. For this purpose, a randomized controlled trial is performed. We expect to have improvements in terms of pain, work ability, patient compliance, and acceptance in our intervention compared to the standard program.

The study helps to ensure that particularly patients living far away from clinical rehabilitation centers receive individualized care.

Because the intervention consists of individualized programs (unimodal, multimodal, and their corresponding intervention modules) for different patient risks, we also expect to have a better response in other outcome measures such as health-related quality of life, subjective well-being, and sensation of pain. We will also explore whether changes in the outcomes occur within the intervention group (unimodal vs multimodal) and how these differences unfold over the follow-up measures. Regarding the comparison between these subgroups, the power of our study is here limited, since our sample size is only intended to compare the two randomized groups (main objective). Nonetheless, this study contributes to the research regarding integrative programs. The exercises and tasks of the program involved in the study are of value, since up to now, only limited data provide information on training individualization. Furthermore, implementation of psychosocial risk factors in low back pain research is limited [57].

One strength of the study is the relatively big sample size and the ability to include patients’ profiles from clinics in six different federation states in Germany. Accordingly, it will be possible to contemplate an external generalizability of the results in Germany. At the same time, the heterogeneity of the study population might limit the internal data interpretation. Sensitivity analyses are planned to consider the effect of covariates. Further, a common limitation of a behavioral intervention including exercises is the impossibility to blind the study staff delivering the intervention and participants to the group allocation; still, the participants are not aware of the study objective. Another limitation is our concealment mechanism: due to constraints of resource management, we are not able to send one randomization number each time, but a few randomization numbers all at once. This could allow a risk of selection bias, because at times, the therapist can predict the next participant group allocation.

The present study provides a feasible individualized program, accessible at home with low costs. One impact of this study is to provide more available rehabilitation aftercare programs to rural populations with different psychosocial risks.

### Trial status

Protocol version 3, Date 19.10.2021.

The study protocol is registered in the German Clinical Trials Register (DRKS) DRKS00020373.

Participant’s recruitment started on 21.09.2020 and is estimated to be completed by December 2022.

## Data Availability

The datasets [generated] for this study should be available in the future, after completion of the trial [doi is requested at the University of Potsdam].

## Abbreviations

LBP: Low back pain
RSI: Risk Stratification Index
RPI-S: Risk Prevention Index
RCT: Randomized controlled trial
IRENA: Intensified Rehabilitation Aftercare Program
TRENA: Training Therapeutic Rehabilitation Aftercare Program
Reha-Sport: Rehabilitation Sport Program
ICD-10: International Classification of Diseases, Tenth Revision
DRV: German Pension Insurance
SMT: Sensorimotor training program
BT: Behavioral therapy modules
AE: Adverse event
SAE: Serious adverse event
T0…T3: Time points
CPG: Chronic Pain Grade Questionnaire (German version)
CPI: Characteristic pain intensity
WAI: Work Ability Index
SPE: Subjective prognosis of gainful employment
DISS: Disability Score
SF-12: 12-Item Short-Form Health Survey
IPAQ: International Physical Activity Questionnaire
BPI: Brief Pain Inventory
TICS: Trier Inventory for Chronic Stress
POMS: Profile of Mood States
VE: Vital exhaustion
HADS: Hospital Anxiety and Depression Scale (German version)
FABQ-D: Fear Avoidance Beliefs Questionnaire (German version)
BSSS: Berlin Social Support Scales
ILE: Life-changing events
CoP: Center of pressure
LPR: Lumbo-pelvic ratio
RoM: Range of motion
TUG: Timed Up and Go Test
DSGVO: General Data Protection Regulation of the European Union
DRKS: German Clinical Trials Register
MLU: Martin-Luther-University of Halle-Wittenberg
